### Sample size

As there is no literature reference to calculate the sample size of DLI treated by sitting lumbar rotation manipulation, and few clinical and statistical assumptions supporting the sample size calculations, so this study is an exploratory study. No references for the experience accumulation method indicated, so we selected 60 cases of small sample.

### Statistical analysis

An independent statistician will use the SPSS V.25.0 software to perform the statistical analysis. Count data and grade data will be described by the number of case. The counting data will be tested by χ^2^; Wilcoxon rank-sum test will be applied to rank data. The measurement data will be statistically described with mean ± standard deviation. In group comparison, paired sample t-test will be applied. The rank sum test will be used for the difference comparison between groups. *P* < 0.05 will be considered statistically significant.

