## Method/design

### Study design

According to the random number table method [13], a total of 60 patients with DLI will be divided into sitting lumbar rotation manipulation group (the intervention group) and supine lumbar traction group (the control group), 30 cases in each group. DLI patients will be numbered according to the visit time, and any one number in the random number table will be selected as the starting point. A random number corresponding to each patient will be obtained along the same direction. Divide this number by 2, and the remainder of 0 will be the intervention group, and the remainder of 1 will be the control group. Two residents participating in this study will be responsible for generating the allocation order sequence.

The treatment of the two groups lasted for 3 weeks. The manipulation of the intervention group would be carried out once every other day, three times a week, a total of 9 times; the control group would be given lumbar traction once a day, five times a week, a total of 15 times. JOA [14] and VAS [15] scores will be recorded as the primary outcomes before the treatment and at the 1st, 3rd, 5th, 8th, 10th, 12th, 15th, 17th, and 19th days after the first treatment and follow-up visit at the 1st, 3rd, and 6th months. JOA [14] efficacy evaluation standard will be used to evaluate the overall efficacy as the secondary outcomes. When analyzing the results, the personnel who collect the data are blind to the grouping situation. The flow of this clinical trial is shown in Fig. 1; the schedule of enrolment, assessments, and interventions is presented in Table 1. JOA [14] and VAS [15] scores are presented in Table 2 and Fig. 2.

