### Outcome assessment

Variables for this clinical trial included the patient’s baseline, primary, and secondary outcomes.

The baseline will be completed before treatment, and the primary and secondary results will be measured at baseline and on the 1st, 3rd, 5th, 8th, 10th, 12th, 15th, 17th, and 19th days after the first treatment, and followed up at the 1st, 3rd, and 6th months. All primary and secondary outcomes will be evaluated by experienced doctors at Wangjing Hospital, and patient allocation results will be blind to them.

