## Discussion

Instability caused by lumbar degeneration is often seen in clinical diagnosis and treatment. Due to the narrowing of the intervertebral space, the lateral recess is relatively narrow. At the same time, the degeneration can cause the movement fulcrum of lumbar vertebrae to move back to the facet joint, making the facet joint degenerate and thicken, the facet joint subluxate, resulting in the narrowing of the lateral recess and spinal canal, the corresponding narrowing of the nerve root outlet, and stimulating the nerve root to produce back pain and other symptoms. These changes are aggravated during exercise, and symptoms such as low back pain and leg pain are aggravated when nerve roots are stimulated.

In order to ensure the effective and complete data, but also to protect the interests of the subjects, we will improve the compliance of the subjects from the following aspects. (a) When the subjects were screened, more telephone numbers of their family members were left to facilitate communication. During the experiment, all the questions will be answered in time, and the information will be collected and reported to the researchers. (b) Make the appointment of project examination, the preparation of application form and the record of data in advance to ensure that the subjects can enter the treatment course in time. Patiently explain the possible complications in the treatment, and tell the subjects not to be nervous once this happens, and the doctor will take necessary measures. (c) Humanistic care. During the manipulation, patients’ nervous mood will be appeased, and appropriate psychological comfort will be given, especially for older subjects. When it is time for treatment, telephone notice or SMS greetings will be given in advance. During the treatment, the patient’s condition will be continuously observed and reported to the researcher when necessary. At the same time, we will promote participant retention and compete follow-up in the above ways.

If the subjects could not complete the whole process of the trial due to any reasons, the reasons for their withdrawal should be recorded in detail. At the same time, attention should be paid to these patients for further observation and treatment within a certain period of time to protect the safety of patients after withdrawal from the trial. For the missing data processing, multiple imputation (MI) method [22] will be used to complete the missing data.

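### Within-arm paired t-tests cannot test the hypothesis against traction, and the unadjusted rank-sum test between arms gives up precision and plans no difference with a confidence interval

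*Protocol article*

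**What the plan says.** The Statistical analysis section of the protocol article names the tests. For measurement data: "The measurement data will be statistically described with mean ± standard deviation". Then: "In group comparison, paired sample t-test will be applied", and "The rank sum test will be used for the difference comparison between groups". The only decision rule is that P below 0.05 "will be considered statistically significant". The section names no covariate, no visit, no model across visits, and no between-arm difference or interval.

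Under Study design, the JOA and VAS "scores will be recorded as the primary outcomes before the treatment and at the 1st, 3rd, 5th, 8th, 10th, 12th, 15th, 17th, and 19th days". Outcome assessment repeats the treatment-period visits and adds that patients are "followed up at the 1st, 3rd, and 6th months". That makes one baseline and 9 + 3 = 12 later visits for each of two primary scores.

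The last paragraph of the Introduction states a comparative hypothesis: manipulation improves symptoms, signs and activity limitation relative to supine traction. Sample size gives 60 patients without a calculation and calls the study exploratory. The Discussion states that the "multiple imputation (MI) method [22] will be used to complete the missing data".

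**The concern.** The hypothesis is about a difference between arms, but half of the stated analysis for the primary scores tests change within each arm. Both arms receive an active treatment and, under Intervention, usual care continues in both. A significant change in one arm or in both says nothing about whether manipulation does better than traction. Separate within-arm P values invite the reading that one treatment worked and the other did not.

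The other half, the rank-sum test, takes one value per patient and adjusts for nothing, although a baseline score is scheduled for everyone. In a sample fixed at 60, part of the available precision is left unused. A trial that calls itself exploratory because it found no data to plan from should mainly deliver an estimated difference with its uncertainty. The stated plan delivers arm means, SDs and P values.

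**Working it through.** **There is no planned figure to reproduce.** The 60 patients were chosen without an effect size, SD or power target.

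**Inputs from the protocol.** 30 per arm (Study design); significance level 0.05 (Statistical analysis; taken as two-sided, which is not stated); baseline plus 12 later visits.

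**Assumed inputs, not in the documents.** True difference 0.5 SD at a single visit; baseline-outcome correlation ρ of 0.3, 0.5 and 0.7; normal scores with equal SD in both arms.

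**Step 1: what the paired tests can show.** Suppose ρ = 0.5 and both arms improve by the same 0.5 SD. The SD of change is √(2(1 − 0.5)) = 1 SD, so the paired t-statistic in each arm is about 0.5 × √30 = 2.74 on 29 degrees of freedom, against a critical value of about 2.05. Both arms are then significant while the true difference between them is zero.

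**Step 2: variance of the between-arm comparison, relative to unadjusted post scores.**
- Change scores: 2(1 − ρ) = 1.40 / 1.00 / 0.60.
- ANCOVA: 1 − ρ² = 0.91 / 0.75 / 0.51.

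ANCOVA is the smallest at each ρ. At ρ = 0.3 change scores do worse than ignoring baseline (1.40 against 1).

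**Step 3: difference detectable with 80% power (normal approximation).** For a comparison of post-score means: (1.960 + 0.842) × √(2/30) = 0.72 SD. The rank-sum test has efficiency 3/π under normality, so its figure is 0.723/√(3/π) = 0.74 SD. For ANCOVA, multiply 0.723 by √(1 − ρ²): 0.69 / 0.63 / 0.52 SD.

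**Step 4: simulated power with the rank-sum test itself.** There were 4,000 simulated trials for each ρ. Monte Carlo standard error is at most √(0.25/4000) = 0.8 percentage points.

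| Analysis | ρ = 0.3 | ρ = 0.5 | ρ = 0.7 |
|---|---|---|---|
| Rank-sum, post scores | 44% | 45% | 44% |
| Rank-sum, change scores | 35% | 45% | 66% |
| ANCOVA | 51% | 58% | 74% |

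ANCOVA gains 7 / 13 / 30 points over rank-sum on post scores and 16 / 13 / 8 points over rank-sum on change scores. The ordering does not depend on which reading of the planned test is right; the size of the gain does.

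**Step 5: equivalent sample size.** ANCOVA matches the precision of a 60-patient unadjusted comparison of means with 60 × (1 − ρ²) = 55 / 45 / 31 patients.

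**The case against.** The case for the plan is substantial, and much of it stands.

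- **A reader might infer that the collected baseline is discarded.** The text does not establish this. The comparison of differences may mean change from baseline, and baseline also enters the paired tests and the JOA improvement rate. Neither reading adjusts for baseline.
- **A reader might infer that a rank-based result cannot be combined with multiple imputation.** That goes too far. The Mann-Whitney probability has a standard error and can be pooled, and a Hodges-Lehmann shift with an interval can accompany the test. The protocol names neither.
- **A reader might see a fault in using a t-test within arms and ranks between arms.** This is weak. A paired t-test needs roughly normal differences, not normal raw scores, and a rank test is defensible for whole-number VAS marks and a summed ordinal JOA.
- **A reader might infer a false-positive problem from chance baseline imbalance.** Randomisation protects the rank-sum test; imbalance costs precision.
- **A condensed article may leave estimates and models to an analysis plan.** Silence alone would be no finding. Here the article states which tests are used for which comparison, and the point is that those tests fit the hypothesis and the design badly.
- **The study is exploratory with no power target**, so lower power contradicts no promise. That reduces the weight of the power figures but strengthens the case for an estimate with an interval.

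One further caution concerns the remedy: an unstructured covariance over 12 visits has 12 × 13/2 = 78 parameters, which is too many for 60 patients.

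**Conclusion.** The point holds as a matter of efficiency and estimation. The within-arm paired t-tests cannot address the comparative hypothesis; that follows from the text alone and needs no assumption. The unadjusted rank-sum test is valid but less efficient than ANCOVA under both readings of what it is applied to, and no between-arm difference with a confidence interval is planned.

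The size of the loss is uncertain. For an assumed 0.5 SD difference it runs from 7 to 30 percentage points of power against post scores and from 8 to 16 against change scores, for correlations from 0.3 to 0.7. Neither the effect size nor the correlations come from the documents, and normal scores are also assumed. The documents do not support a claim that the planned test is invalid or inflates type I error. The change is one that should be made, not one without which the trial fails.

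**What to change.** In the Statistical analysis section, replace the between-arm sentence for JOA and VAS with one of these:

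1. ANCOVA of each primary score at one visit, named before comparative data are examined, with arm and baseline score as terms. The protocol names no such visit at present, so the choice has to be made and recorded.
2. A mixed model across visits with arm, visit, arm-by-visit and baseline score, and a parsimonious covariance structure stated in advance.

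Report the adjusted between-arm difference with its 95% CI. This estimate and its standard error also pool directly under the planned multiple imputation. Keep the rank-sum test as a sensitivity analysis and state whether it uses post scores or change scores. Report within-arm change descriptively, and say that it will not support conclusions about efficacy.

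The cost is a change of wording and slightly more modelling work, with no new data. The price is an approximate-normality assumption for two bounded scores, which the retained rank-sum test helps to check.

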### Data collection and management

The outcome assessors will use the CRF papers to collect the data. The CRF papers will be randomly put into envelopes of different groups and sent to a researcher who is responsible for electronic data input. Then, the researcher will transcribe the CRF into an electronic data acquisition system (EDC), which is a free Research Manager named ResMan (http://www.medresman.org) provided by the China Clinical Trial Registry and meets the available standards for security. Every subject will be assigned a separate experiment identification number, and the relevant data will be strictly confidential. Only members of the trial will have access to the data set. Anonymized trial data will be shared with other researchers to enable international prospective meta-analyses. The research data will be stored in the EDC system in a separate password-protected location. Data Monitoring Committee was not considered as this is a low-risk intervention.

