**Table 1 Tab1:**
[figure not shown]
Schedule of enrolment, interventions, and assessments

**Table 2 Tab2:** The JOA [14] scoring system for assessment of low back pain. The score in a normal subject is the total of the best scores: (I+II+III+IV) = 29 points

Parameter	Finding	Score (points)
I. Subjective symptoms (9 points)		
a. Low back pain	None	3
	Occasional mild pain	2
	Frequent mild/occasional severe pain	1
	Frequent pain/continuous pain	0
b. Leg pain and/or tingling	None	3
	Occasional slight symptoms	2
	Frequent slight symptoms/occasional severe symptoms	1
	Frequent severe symptoms/continuous severe symptoms	0
c. Gait	Normal	3
	Able to walk > 500 meters although it results in pain tingling and/or muscle weakness	2
	Unable to walk > 500 meters owing to leg pain tingling and/or muscle weakness	1
	Unable to walk > 100 meters owing to leg pain tingling and/or muscle weakness	0
II. Clinical signs (6 points)		
a. Straight leg raising (includes a tight hamstring)	Normal (> 70°)	2
	30° to 70°	1
	< 30°	0
b. Sensory disturbance	None	2
	Slight disturbance (not subjective)	1
	Marked disturbance	0
c. Motor disturbance	Normal (Grade 5)	2
	Slight weakness (Grade 4)	1
	Marked weakness (Grades 0 to 3)	0
III. Restriction in activities (14 points)		
a. Turn over while lying	No restriction	2
	Moderate restriction	1
	Severe restriction	0
b. Standing	No restriction	2
	Moderate restriction	1
	Severe restriction	0
c. Washing	No restriction	2
	Moderate restriction	1
	Severe restriction	0
d. Leaning forward	No restriction	2
	Moderate restriction	1
	Severe restriction	0
e. Sitting about 1 h	No restriction	2
	Moderate restriction	1
	Severe restriction	0
f. Lifting or holding a heavy object	No restriction	2
	Moderate restriction	1
	Severe restriction	0
g. Walking	No restriction	2
	Moderate restriction	1
	Severe restriction	0
IV. Urinary bladder function (−6 points maximum)	Normal	0
	Mild dysuria	-3
	Severe dysuria	-6

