### Randomization, allocation concealment, and blinding

Upon completion of the baseline assessment, participants were randomly assigned by the physician to the sitting lumbar rotation manipulation group and the supine lumbar traction control group. Because doctors and patients are able to know which kind of intervention will be accepted, they cannot be blind to the treatment, but the result evaluator and data statistician are blind to the grouping and treatment.

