#### Primary outcomes

We will use the Japanese Department of orthopedics Association (JOA [14]) low back pain rating scale (Table 1) to observe and record the symptom and sign scores of the two groups of patients at each visit point. The parameters in the scoring table are divided into four parts. The maximum score is 29 points, and the minimum score is −6 points. The higher the score the more normal the patient’s overall status. VAS [15] will be used to observe and record the pain degree of each visiting point in the two groups (Fig. 2), which means marking the numbers 0–10 with a straight line divided into 10 equal parts, according to the patient’s degree of pain to determine and draw on the corresponding number, and finally by the doctor according to the patient’s mark on the scale of the number to score. If the patient is marked on 5, it will be recorded as 5 points.

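### Filing assessor-completed CRFs in group envelopes is inconsistent in itself and puts the promised blinding at risk; the VAS and the patient-reported JOA items should be described as reports from unblinded patients

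*Protocol article*

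**What the plan says.** Under Data collection and management, the Protocol article first states who fills in the forms: "The outcome assessors will use the CRF papers to collect the data". The next sentence says what happens to them: "The CRF papers will be randomly put into envelopes of different groups and sent to a researcher". That researcher transcribes them into the electronic system. The same section gives every subject a separate identification number.

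Blinding is promised in three places.
- Randomization, allocation concealment, and blinding, on doctors and patients and then on those who are masked: "they cannot be blind to the treatment, but the result evaluator and data statistician are blind to the grouping and treatment".
- Study design: "When analyzing the results, the personnel who collect the data are blind to the grouping situation".
- Outcome assessment: the hospital doctors who evaluate all primary and secondary outcomes are said to be unaware of the allocation.

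The abstract labels the trial as blind at the level of the outcome assessor. For the VAS, Primary outcomes has the patient judge the pain and "draw on the corresponding number"; the doctor then reads that number off. Table 2 divides the JOA into subjective symptoms (9 points), clinical signs (6), restriction in activities (14) and a bladder item that can only subtract. The secondary outcome is an improvement rate calculated from the JOA.

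**The concern.** The form-handling sentence gives two instructions that cannot both be followed. Forms placed at random are not sorted by group, and forms sorted by group are not placed at random. If they are sorted, somebody between the assessor and data entry must hold the grouping, and the only people the article names before that step are the assessors, who are promised blind.

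Patients and treating doctors are unblinded, so masking of the assessor and the statistician is all the masking this trial has. If the person who files the forms also assesses, knowledge gained at filing could carry into later scoring of the same patient. Batches split by arm could also allow queries or corrections at data entry to differ between arms.

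A second matter bears on how the results are read. A blinded assessor cannot remove the influence of a patient's own knowledge of treatment on what the patient reports, and much of the primary outcome information is, or may be, patient report.

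**Working it through.** **Form handling: the statements side by side**

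| Role | Blinding promised? | Contact with the forms |
|---|---|---|
| Outcome assessor / data collector | Yes (Study design; Randomization, allocation concealment, and blinding; Outcome assessment) | Completes them |
| Person who fills the envelopes | Role not named | Must hold the grouping, by name or by code, if sorting is by group |
| Data-entry researcher | Not clearly covered by any promise | Receives the envelopes |
| Statistician | Yes (Randomization, allocation concealment, and blinding) | Not described |

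1. If the assessor fills the envelopes and they show the treatment, the blinding promises are contradicted.
2. If someone else fills them using a neutral code, the promises can all be kept. The forms are still split by arm, though, so learning one patient's treatment reveals it for every form in that envelope.
3. If placement really is random, the envelopes carry no information on group and serve no purpose.
4. In every case the identification number already links a form to its patient, so sorting by group has no stated use.

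**How often the rule applies**

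Assessments per patient: 1 baseline + 9 in the treatment period (days 1, 3, 5, 8, 10, 12, 15, 17, 19) + 3 follow-ups (months 1, 3, 6) = 13. For 60 patients: 13 × 60 = 780 planned assessments. After the day 1 assessment, 8 + 3 = 11 assessments of the same patient remain. The article does not say whether forms are filed as they accrue or at the end. Only the first would let knowledge from filing reach later scoring.

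**Share of the primary outcomes that comes from patients**

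The article's own maximum is reproduced first from the item scores in Table 2: part I 3 × 3 = 9, part II 3 × 2 = 6, part III 7 × 2 = 14, part IV 0 at best. 9 + 6 + 14 + 0 = 29, as stated.

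Share = points counted as patient-reported / 29:

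| Counted as patient-reported | Points | Share |
|---|---|---|
| Part I only (the part the table labels subjective) | 9 | 31% |
| Low back pain, leg symptoms, washing and sitting about 1 h only | 3 + 3 + 2 + 2 = 10 | 34% |
| Parts I and III, less gait and walking | 23 − 3 − 2 = 18 | 62% |
| Parts I and III, less gait | 23 − 3 = 20 | 69% |
| Parts I and III | 9 + 14 = 23 | 79% |

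Part II, the examined signs, is 6/29 = 21%. The VAS is wholly patient-marked, and this needs no assumption.

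**The case against.** The strongest defence is that nothing in the article shows a breach. The sorter is not named, sorting follows completion of the form, the envelopes may bear a neutral code, and the one named recipient, the data-entry researcher, is not promised blind. Coded envelopes filled by a third person would satisfy every promise. This stands, and it rules out several stronger conclusions that a reader might draw:

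- *The blinding is broken, and every form reaches data entry with the arm visible.* That needs envelopes that show the treatment, which the text does not say.
- *Random filing would put wrong arm labels in the data.* That needs the arm to be read from the envelope. The article gives each subject an identification number and nowhere says that the envelope determines the arm.
- *The assessor-blind label is false.* The label describes the assessors, and the article says openly that patients and treating doctors cannot be masked. Manipulation and traction cannot be hidden from those who receive them.
- *Four fifths of the JOA is unblinded patient report.* The table calls only part I subjective and does not say how part III is obtained. The 79% is the upper end of a range that starts at 31%.

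The defence does not remove the conflict in the form-handling sentence. That sentence is an explicit rule, not a detail left to a fuller document, and its two halves disagree. Nor does a neutral code justify splitting the forms by arm when trial numbers are already in use.

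**Conclusion.** The concern holds as an inconsistency that puts blinding at risk, not as a demonstrated breach. The form-handling rule contradicts itself and sits badly with the blinding promised for assessors, data collectors and statistician. It governs all 780 planned assessments. Whether any assessor would in fact be unmasked depends on three things the article does not state: who fills the envelopes, what they are labelled with, and when filing takes place.

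The patient-report point is a limitation to be stated, not an error. One primary outcome, the VAS, comes entirely from unblinded patients. For the other, the JOA, the share is 31% if only part I is counted and up to 79% if all of part III is reported as well. The secondary outcome, being calculated from the JOA, carries the same limitation. No size of bias can be derived from the document, and none is claimed.

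**What to change.** 1. Delete the group envelopes. Send all CRFs to data entry in one stream identified only by trial number, which the section already assigns.
2. Keep the allocation code outside the database until lock, then merge it. Merging it as a neutral arm code keeps the statistician blind during the analysis.
3. Name who files the forms, and state whether the data-entry researcher is blind.
4. In the description of the outcomes, say that the VAS and the patient-reported JOA items come from patients who know their treatment, and say which part III items are asked and which are observed.
5. Optionally, show the JOA part II subscore (6 points) as a supportive result that rests on blinded examination.

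Items 1 to 4 are changes of wording and form routing with no extra staff or visits. Item 5 adds one table from data already collected.
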